# A randomized controlled trial testing a hyaluronic acid spacer injection for skin toxicity reduction of brachytherapy accelerated partial breast irradiation (APBI): a study protocol

**DOI:** 10.1186/s13063-018-3035-3

**Published:** 2018-12-17

**Keywords:** Breast neoplasms, Partial breast irradiation, Brachytherapy, Permanent breast seeds implant, Skin toxicity reduction, Telangiectasia, Spacer, Hyaluronic acid

## Abstract

**Background:**

Accelerated partial breast irradiation (APBI) is a treatment option for selected early stage breast cancer patients. Some APBI techniques lead to skin toxicity with the skin dose as main risk factor. We hypothesize that a spacer injected between the skin and target volume reduces the skin dose and subsequent toxicity in permanent breast seed implant (PBSI) patients.

**Methods:**

In this parallel-group, single-center, randomized controlled trial, the effect of a subcutaneous spacer injection on skin toxicity among patients treated with PBSI is tested. Eligibility for participation is derived from international guidelines for suitable patients for partial breast radiotherapy, e.g. women aged ≥ 50 years with a histologically proven non-lobular breast carcinoma and/or ductal carcinoma in situ (DCIS), tumor size ≤ 3 cm, node-negative, and PBSI technically feasible. Among exclusion criteria are neoadjuvant chemotherapy, lymphovascular invasion, and allergy for hyaluronic acid. For the patients allocated to receive spacer, after the PBSI procedure, 4–10 cc of biodegradable hyaluronic acid (Barrigel™, Palette Life Sciences, Santa Barbara, CA, USA or Restylane SubQ®, Galderma Benelux, Breda, the Netherlands) is injected directly under the skin using ultrasound guidance to create an extra 0.5–1 cm space between the treatment volume and the skin. The primary outcome is the rate of telangiectasia at two years, blindly assessed using Bentzen’s 4-point scale. Secondary outcomes include: local recurrence; disease-free and overall survival rates; adverse events (pain, redness, skin/subcutaneous induration, radiation dermatitis, pigmentation, surgical site infection); skin dose; cosmetic and functional results; and health-related quality of life.

A Fisher’s exact test will be used to test differences between groups on the primary outcome.

Previous studies found 22.4% telangiectasia at two years. We expect the use of a spacer could reduce the occurrence of telangiectasia to 7.7%. A sample size of 230 patients will allow for a 10% lost to follow-up rate.

**Discussion:**

In this study, the effect of a subcutaneous spacer injection on the skin dose, late skin toxicity, and cosmetic outcome is tested in patients treated with PBSI in the setting of breast-conserving therapy. Our results will be relevant for most forms of breast brachytherapy as well as robotic radiosurgery, as skin spacers could protect the skin with these other techniques.

**Trial registration:**

Netherlands Trial Register, NTR6549. Registered on 27 June 2017.

**Electronic supplementary material:**

The online version of this article (10.1186/s13063-018-3035-3) contains supplementary material, which is available to authorized users.

## Background

Breast cancer is increasingly diagnosed at an early stage [1, 2]; for that stage, breast-conserving therapy, which includes wide local excision and radiotherapy, is equivalent to mastectomy in terms of local control and overall survival [3, 4]. These oncological outcomes are excellent in early-stage breast cancer patients [2]. Hence, radiotherapy essentially provides a cosmetic and quality-of-life benefit over mastectomy [5]. Since local recurrences usually occur close to the primary tumor [6], the concept of accelerated partial breast irradiation (APBI) was introduced [7] to both reduce the amount of breast tissue irradiated and enable faster treatment. For well-selected patients, APBI has been tested and validated through large randomized clinical trials (RCT), using either brachytherapy [8–11], external 3D conformal radiotherapy [12, 13], or intraoperative radiotherapy [14, 15].

Brachytherapy has been the most evaluated technique and recent advances beyond multicatheter implantation include balloon or strut brachytherapy as well as permanent breast seed implants (PBSI) [16, 17]. Brachytherapy is generally well tolerated and reported long-term toxicities are acceptable. A lower incidence of low-grade acute skin toxicity for APBI, 21% vs 86% for whole breast radiotherapy (*p* < 0.001) has been reported for the GEC-ESTRO trial [18]. Regarding late side effects at five-year follow-up, lower rates of severe grade 2–3 skin, 6.9% vs 10.7%, and similar rates of subcutaneous side effects, 12.0% vs 9.7%, were found in this study [19]. On the other hand, in a retrospective analysis of 1034 breast patients treated at The Ohio State University including 31% treated with a balloon applicator, Wobb reported more seroma grade 2 or higher (14.4% vs 2.9%, *p* < 0.001), more painful fat necrosis (10.2% vs 3.6%, *p* < 0.001), and more telangiectasia grade 2 or higher (12.3% vs 2.1%, *p* < 0.001) for APBI compared to whole breast radiotherapy [20]. Among those permanent side effects, increased painful seroma is almost exclusively due to balloon applicator, fat-necrosis can be due to multiple factors, while telangiectasia is almost exclusively due to an excess of dose to the skin. This makes telangiectasia a specific marker of radiation toxicity [21, 22]. Telangiectasia corresponds to the dilation of an abnormal neo-vasculature in the skin following the destruction of normal capillaries by the radiation treatment, resulting in visible vessels [23]. Although rates are lower than with whole breast irradiation, in breast brachytherapy 10–27% [9, 19, 24] of the patients develop some grade of telangiectasia. The majority of lesions are grade 1 (< 1 cm^2^) in breast radiotherapy studies reporting on late skin toxicity [9, 25, 26]. The onset of telangiectasia is from six months to 10 years after radiotherapy delivery [23]; however, rates of telangiectasia peak at two years with PBSI. Although permanent in most cases, some authors report disappearing of the telangiectasia with longer follow-up [9, 27]. Nevertheless, if present, telangiectasia can remind patients of their cancer similar to a surgical scar and have a direct negative impact on the cosmetic outcomes [9, 26].

Several authors recommend keeping a distance of at least 5 mm between the planning target volume (PTV) and the skin [28, 29] and limiting the maximum skin dose to 70% [8]. However, such constraints are not always achievable. A simple solution would be the use of a spacer material injected subcutaneously to move the skin out of the high dose region [21].

In this manuscript, we report the protocol of a RCT investigating the clinical benefit of a subcutaneous spacer injection on the skin dose, late skin toxicity, and cosmetic outcome in patients treated with low dose rate (LDR) seed brachytherapy. For this study, the breast skin is considered as a critical structure for the radiotherapy and the clinical outcomes are measured using a breakdown of traditional skin toxicity scales in order to capture the toxicity that is specific to radiotherapy [9, 21, 23, 30].

## Methods/design

### Aim and design

We propose a parallel-group RCT comparing the occurrence of telangiectasia at two years in PBSI patients with or without a subcutaneous spacer injection. Allocation ratio is 1:1 and the trial is designed to test the superiority of the intervention. The primary hypothesis for the trial assumes that an injected hyaluronic acid spacer will reduce skin dose of PBSI and eventually the rate of telangiectasia at two years, compared to patients undergoing PBSI without spacer. As the intervention is applied when the patient is sedated, a placebo injection as comparator was deemed unnecessary. The methods section is described according to the Standard Protocol Items: Recommendations for Interventional Trials (SPIRIT) 2013 checklist (see Additional file 1).

Eligible patients will be recruited at hospitals referring patients after breast-conserving surgery for adjuvant radiotherapy at the Erasmus MC Cancer Institute, a large University hospital in Rotterdam, where the PBSI technique can be performed in the Netherlands.

### Eligibility and exclusion criteria

Eligibility criteria were derived from international guidelines [31, 32] for suitable patients for partial breast radiotherapy. Eligible patients are females aged ≥ 50 years with a confirmed histological diagnosis of invasive ductal carcinoma (IDC) and/or papillary, tubular, cribriform or medullar carcinoma and/or ductal carcinoma in situ (DCIS), after breast-conserving surgery with axillary node dissection (with a minimum of six nodes sampled) or sentinel lymph node biopsy. The maximum dominant tumor size is 3 cm and the tumor must be excised with negative surgical margins at ink for invasive carcinoma and ≥ 2 mm negative margins for DCIS or have a negative re-excision. The PBSI should be deemed technically feasible based on the seroma location, visibility, and size performing an ultrasound; the total implanted volume should be < 150 cc. Patient should have signed an informed consent.

Ineligible patients include those with lymphovascular invasion, lobular features on histology (pure or mixed) or sarcoma histology, triple negative tumors, extensive in situ carcinoma, multicentric disease (in more than one quadrant or separated by ≥ 2 cm), bilateral breast cancer, recurrent breast cancer, Paget’s disease of the nipple, metastases or active other cancer (defined by any malignancy in < 5 years, excluding any cured non-melanoma skin cancer or cervical cancer), neoadjuvant chemotherapy, known allergy for hyaluronic acid, active auto immune disorder with severe vasculitis component, uncontrolled and complicated insulin-dependent diabetes, pregnancy, cosmetic breast implants, psychiatric or addictive disorder that would preclude attending follow-up, or postoperative wound infection or abscess following Centers for Disease Control and prevention (CDC) criteria.

### Interventions

The permanent seed implant procedure includes a computed tomography (CT) simulation done positioning the patient similarly to for external beam breast radiotherapy. The clinical target volume (CTV) corresponds to the seroma with a 1-cm margin, limited to the fascia pectoralis, and 5 mm below the skin; the planned target volume (PTV) is an additional expansion of 0.5 cm with the same skin and chest wall limits. A pre-implant plan is generated using the MIM Symphony® software (MIM Software Inc., Cleveland, OH, USA) to order stranded ^103^Pd seeds of 2.5 U activity.

For the procedure, anesthesia includes a non-steroidal anti-inflammatory drug (NSAID) for two days, light sedation with Propofol, and local freezing. Patients are positioned on a breast board, with the arm abducted similarly to the CT simulation. The breast skin is disinfected and the patient draped. The PTV projection perpendicular to the fiducial needle axis is outlined on the skin surface and verified using ultrasound. A PBSI template (Concure Oncology, Seattle, WA, USA) is attached to the fiducial needle and immobilized using a modified medical articulated arm (Fisso, Medtec Baitella Alt, Switzerland). The preloaded needles containing ^103^Pd strands are then inserted under US guidance [33]. In patients allocated to receive spacer, an amount of 4–10 cc of biodegradable hyaluronic acid (Barrigel™, Palette Life Sciences, Santa Barbara, CA, USA or Restylane SubQ®, Galderma Benelux, Breda, the Netherlands) is injected directly under the skin under ultrasound guidance covering the PTV projection, aiming to create an extra 0.5–1 cm space between the treatment volume and the skin. If the skin is judged not to be at risk in all projection quadrants, it could be decided to only inject the area at risk. The injected skin quadrants will be reported specifically. All radiation oncologists involved in this study are trained to perform the intervention and the injection procedure and reporting instructions are incorporated in trial protocols. The hyaluronic acid spacer is expected to be fully degraded after 3–9 months.

### Outcomes

The primary endpoint of this trial is the occurrence of telangiectasia at two years after PBSI. Assessment is performed by a blinded physician, following the Bentzen’s 4-point scale which is included in the LENT/SOMA questionnaire [34, 35]. This scale is defined as: “none;” grade I, “< 1 cm^2^,” grade II, “1–4 cm^2^;” and grade III, “> 4 cm^2^.” Patients will also be blinded for the allocated treatment. The secondary outcomes include the local recurrence rate at five and ten years, the disease-free and overall survival rates at five years, as well as brachytherapy and spacer injection adverse events (AE) according to the commonly used NCI Common Toxicity Criteria for Adverse Events (CTCAE v 4.03) scale for acute side effects [36], practically occurring within three months of the brachytherapy, and the Radiation Therapy Oncology Group (RTOG)/ European Organisation for Research and Treatment of Cancer (EORTC) scoring systems for late side effects [37], practically occurring after three months. The symptoms include the experience of pain, skin redness, pigmentation, induration, dermatitis, subcutaneous induration, and the occurrence of infection at the site of spacer injection. Additionally, patient-reported outcome measures (PROMs) include the cosmetic result with the Breast Cancer Treatment Outcome Scale (BCTOS) questionnaire [38], using a validated Dutch version which will shortly be published by our group [39] and the health-related Quality of Life using the Dutch version EORTC QLQ-C30 and BR23 questionnaires, version 3 [40]. Ipsilateral breast recurrence must be proven getting a copy of the biopsy or the salvage surgery pathology report. Dosimetry outcomes include the PTV volumes receiving at least 100% or 200% of the prescribed dose (V_100_ and V_200_) as quality assurance for all treatment plans and maximum dose to a small skin volume of 2 mm thickness over 1 cm^2^ (D_0.2cc_) [21, 41] and the presence of a hotspot (isodose ≥ 90%) [42] on 1 cm^2^ of the skin as indicators of skin toxicity risk.

Outcomes are collected before the PBSI implantation at baseline, at the end of the procedure, and at two months, six months, and every year up to five years, during follow-up visits at the cancer center. If a patient does not attend a follow-up appointment, she will be called and/or her family doctor contacted. Reason for no-show will be recorded in order to ensure exhaustive capture of survival, recurrence, and/or AEs. Overall and disease-specific survival will be assessed until 10 years through GBA (Population registry, Gemeentelijke Basis Administratie) and/or general practitioners. A summary of the timing of questionnaires is detailed in Fig. 1.

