### Statistical methods

All statistical tests will be two-sided and a *p* value < 0.05 is considered to be significant. Statistical analyses will be performed using IBM SPSS version 24 (IBM Corporation, Armonk, NY, USA). Data will be analyzed following intention-to-treat and per-protocol. Missing data will be handled using multiple imputation. Descriptive statistics will be used for all outcome measures.

A Fisher’s exact test or Chi-squared test will be performed to test the reduction in the rate of telangiectasia in the study groups at two-year follow-up, i.e. to test the hypothesis that the rates of telangiectasia in both study groups are equal (superiority study).

Local recurrence-free survival as well as overall and disease-specific survival rates at five and ten years will be estimated using the Kaplan–Meier method. The local recurrence rate will be reported at five and ten years. A Fisher’s exact test or Chi-squared test will be performed to test the difference in proportions (six-month, one-year and two-year cumulative rate of side effects, skin dose > 90% over at least 1 cm^2^ at post-planning) between groups. (Skin) dosimetry data will be compared using a Mann–Whitney U test or an unpaired Student’s t-test depending of distribution of data. To study the effect of spacer on cosmesis (BCTOS questionnaire) and quality of life (EORTC-QLQ-C30/BR23 and EQ5-D questionnaire) over time, a repeated measurements analysis will be performed (linear mixed model, covariance structure: unstructured) with independent variables time, allocated group, and interaction effects between time and allocated group.

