Other secondary outcomes are brachytherapy and spacer injection AEs according to commonly used NCI CTCAE and RTOG/EORTC scoring systems for late side effects. Where our main hypothesis is that the spacer increases distance and reduces skin dose and telangiectasia, this will allow for analyzing the effect on other less radiotherapy-specific symptoms such as pain, skin redness, pigmentation, induration, dermatitis, subcutaneous induration, and the occurrence of infection at the site of spacer injection. Although hyaluronic acid is widely used as a dermal filler, the application as a skin spacer in patients treated with breast radiotherapy is a new concept and any unexpected side effects will be captured. Skin dose outcomes will potentially lead to updated skin dose constraints in treatment planning. Also, it could distinguish radiotherapy induced toxicity from other causes (i.e. intervention-related toxicity). PROMs assess the effect of the skin spacer on cosmesis, function, and quality of life. Furthermore, by using internationally recognized PROMs, a better comparison with other radiotherapy techniques is possible.

This clinical trial was designed because it is unknown whether the dosimetric benefit of the spacer, which was found in our pre-clinical study [44], translates in a real patient benefit. An example of a clinical trial that could not demonstrate that a dosimetric benefit translates into better patient outcomes, is the breast intensity modulated radiation therapy (IMRT) trial. In this trial, the improved radiation dose distribution and reduced moist desquamation using IMRT, compared to standard wedge RT, did not result in reduced long-term side effects such as chronic breast pain [43].

Our primary analysis will be done following the intention-to-treat principle: the effect of skin spacer on telangiectasia rate at two years. However, a per-protocol analysis will allow for a better definition of a successful skin spacer as the skin spacer injection protocol (> 5 mm in a PTV skin projection area) is not definite and the trial could be hypothesis-generating.

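### The infection outcome has two wordings, and the one in Methods names a site that control patients do not have, so it cannot be assessed alike in both arms

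*Protocol article*

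**What the plan says.** The protocol article words the infection outcome in two ways.

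- **Abstract, Methods.** The adverse events listed as secondary outcomes end with "radiation dermatitis, pigmentation, surgical site infection".
- **Methods/design, Outcomes.** The symptom list ends with "the occurrence of infection at the site of spacer injection".
- **Discussion.** Among the less radiotherapy-specific symptoms on which the spacer's effect is to be analysed, the article again has "subcutaneous induration, and the occurrence of infection at the site of spacer injection".

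Three other sections bear on it.

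- **Interventions.** Every patient has preloaded seed needles inserted in the breast. Only in the spacer arm is there an injection; the gel "is injected directly under the skin under ultrasound guidance covering the PTV projection", and the operator may limit it to the area judged at risk.
- **Aim and design.** There is no sham: "a placebo injection as comparator was deemed unnecessary".
- **Statistical methods.** For the cumulative side-effect rates at six months, one year and two years, "A Fisher’s exact test or Chi-squared test will be performed to test the difference in proportions" between the groups. Infection is not named there.

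**The concern.** A between-arm comparison of a safety outcome needs an event that can be observed in the same way in both arms. Pain, redness, pigmentation, induration and dermatitis meet that requirement as listed. Infection, as worded in Outcomes and the Discussion, is the one item tied to a site that exists in only one arm.

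An assessor who follows that wording has no place to record an infection of the implant area in a control patient. The same infection in a spacer patient would qualify if it lay under the injected skin. Infections caused by the needle implant alone could then be counted in one arm and not in the other.

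This matters because the Discussion calls the skin spacer a new concept in breast radiotherapy and hopes to separate radiotherapy-induced toxicity from toxicity due to the intervention. For infection, that separation depends on a control rate measured in the same way.

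**Working it through.** **1. The plan's own figure.** The article gives no infection rate and no calculation for infection. The only planning figure used here is the 105 patients per arm in Sample size. It reproduces: two proportions of 22.4% and 7.7%, two-sided alpha 0.05 and power 80% with continuity correction give 105 per arm, and exact Fisher power at 105 per arm is 81.7%. It concerns telangiectasia and serves below only as the arm size.

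**2. Can each wording be scored in each arm?**

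| Wording | Where | Spacer arm | Control arm |
|---|---|---|---|
| Surgical site infection | Abstract | yes | yes |
| Infection at the spacer injection site | Outcomes, Discussion | yes, within the injected area | no such site |

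**3. Illustration under literal scoring.** Assume that (a) control patients are scored as zero, (b) every implant-area infection in the spacer arm counts, and (c) the true infection rate π is the same in both arms. None of these is stated in the article.

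With k events against 0 and n per arm, the two-sided Fisher p is 2 × C(n, k) / C(2n, k). For n = 105:

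- k = 5: p = 0.0595, not significant
- k = 6: p = 0.029, significant at the plan's two-sided 0.05

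So 6 events (6/105 = 5.7%) are enough. The chance of a false signal of harm is P(X ≥ 6) with X ~ Binomial(105, π). For comparison, the last column gives the chance of p < 0.05, in either direction, when infection is counted in both arms.

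| Assumed π | Expected spacer-arm events, 105 × π | P(X ≥ 6), controls scored zero | Infection counted in both arms |
|---|---|---|---|
| 2% | 2.1 | 1.9% | 0.5% |
| 3% | 3.15 | 9.7% | 1.2% |
| 5% | 5.25 | 42.9% | 2.2% |

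At 115 per arm (half of the planned 230) the threshold is again 6 events (p = 0.029), and the chances with controls scored zero are 2.9%, 13.3% and 51.7%.

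**4. Effect on the estimate.** Under the same assumptions the true risk difference is π − π = 0, while the expected observed difference is π − 0 = π. The overstatement equals the whole control rate. At 2% the test would seldom mislead, but the estimate would still be too high by 2 percentage points.

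**The case against.** A reader might go further and infer that the control infection rate is zero by definition, that the between-arm comparison is therefore invalid, and that the trial cannot estimate the added infection risk. The article does not support this, for these reasons.

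- The infection phrase stands in an open, illustrative list of symptoms. The outcome above it covers adverse events of the brachytherapy as well as of the spacer injection. An infection after seed implantation in a control patient is a brachytherapy adverse event and could be recorded as one. Nothing says that control infections go unrecorded.
- The abstract already supplies an arm-neutral name.
- Statistical methods tests side-effect rates in general and states no infection-specific test. A rate described in the spacer arm alone would be a legitimate safety summary.
- Because the injection may be limited to the area at risk, with the injected quadrants recorded, not every implant infection in the spacer arm would count even on the literal wording.
- The case report form and the full protocol are not shown and may define infection properly.

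These arguments remove the forced zero and the charge of invalidity, and they reduce the probabilities above to an illustration. They leave the inconsistency between the abstract and the Methods and Discussion. Nor do they make a spacer-arm-only summary the natural reading, because the Discussion places infection among the symptoms on which the spacer's effect will be analysed, and that calls for a comparison.

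**Conclusion.** The point holds as an inconsistent outcome definition. One secondary safety item has an arm-neutral wording in the abstract and an arm-specific wording in Outcomes and the Discussion. The arm-specific wording cannot be assessed alike in both arms. If it were applied literally in the planned side-effect comparison, the infection result would be biased against the spacer.

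The size is unknown, because the documents give no infection rate. Under literal scoring with controls at zero and equal true rates, the chance of a false finding of harm at 105 per arm runs from about 2% (true rate 2%) through 10% (3%) to 43% (5%). These figures rest on assumed rates and on scoring that the article does not prescribe. They show why the wording should be settled and do not predict what the trial will report.

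The primary endpoint, its analysis and the sample size are unaffected.

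**What to change.** In Outcomes and in the Discussion, define infection identically for both arms and in line with the abstract, for example as infection at the implant or surgical site of the treated breast after the procedure. Use that definition for the between-arm comparison. Report whether an infection lay within an injected quadrant as a descriptive item in the spacer arm only; the injected quadrants are already to be recorded.

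The exclusion criteria already refer to CDC criteria for postoperative wound infection. Using them here too would be convenient but is not essential.

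Check the case report form and data entry instructions against the new wording. If they already record infection in the same way for both arms, only the text has to be aligned. The cost is one line in the outcome definition and at most one form item, with no added visits. Because enrolment has begun, infections already recorded in either arm should be checked against the single definition.
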